### Eligibility criteria

2.2

Only healthy participants can take part in the study. The detailed inclusion and exclusion criteria are listed in Table 1.

**TABLE 1 pai70147-tbl-0001:** Inclusion and exclusion criteria for Group A or Group B.

Inclusion criteria	Exclusion criteria
For the infant	For the infant
Healthy, full‐term born infants Positive family history for atopic diseases (at least one parent or sibling suffers from atopic diseases such as atopic eczema, food allergy, allergic rhino conjunctivitis, allergic asthma)	Previously consumed hen's egg, peanut, or hazelnut^a^ Suffering from a medically diagnosed wheat allergy
For the caregiver	For the caregiver
No food allergies to hen's egg, cow's milk, peanut, wheat, or hazelnut No (acute, sub‐chronic, or chronic) infectious diseases (including caries) according to physician's decision Mental and linguistic capability to follow the protocol requirements	Any reported disease or medical condition (for example, but not limited to, severe concurrent disease, infection, open wounds in the mouth, comorbidity, for example, acute trauma, serious oncological disease, serious renal disease, relevant cardiovascular disease, autoimmune diseases) or reasons that may, in the opinion of the study physician, interfere with the ability to participate in the study, cause undue risk, or complicate the interpretation of data concerning child or caregiver

^a^
Previous consumption of cow's milk, for example, as infant formula, is allowed since infant formula is commonly produced using cow's milk and formula‐fed infants should not be excluded.

Please see Appensix S1 for further information.

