Group B – Non‐randomized reference: Solids will be introduced with reference to current feeding recommendations^17^, ^21^ based on the parents' decision but without pre‐chewing. Study participants will be invited for the end of study visit (V5) around the child's first birthday.

V5 solo consists only of V5 in Group B (and optional V6); participants will not have been enrolled before. This group serves as an additional reference group, as participants will not have been informed (biased) about premastication before.

At V1 and V5, blood samples from the infant will be collected and stored for allergy diagnostics (including food‐specific IgE and IgG4 to hen's egg, cow's milk, peanut, hazelnut, Ara h 2, Cor a 14, and wheat).

At V5 (or V5 solo), infants will be skin prick tested with hen's egg, cow's milk, hazelnut, and peanut.

In case of the detection of a food‐specific sensitization (elevated food‐specific IgE (>0.1 kU/L) or positive Skin Prick Test, SPT (wheel size >3 mm)) at V5, a double‐blind, placebo‐controlled oral food challenge (DBPCFC) will be offered for evaluation of clinical relevance (optional visit V6). Consequently, parents will be advised to continue feeding the study product until the DBPCFC is performed.

Importantly, apart from the intervention with the ground biscuit in group A, there are no further dietary restrictions imposed by the study protocol for both of the study groups.

All participants may continue their usual medications, as well as those taken for any concomitant diseases, including wheezing and eczema, throughout the study. All subjects who will undergo a DBPCFC will be advised to discontinue oral antihistamines 3–5 days before their appointment. For a detailed description of all study procedures, see Table 3.

**TABLE 3 pai70147-tbl-0003:** Schedule of Events: (a) Group A and (b) Group B.

Visit/Phone call	Enrolment/Screening		Intervention period							V5	(V6)^a^	Unscheduled visit^b^
	V0 (optional)	V1	PC 1	V2	PC2	V3	PC3	V4	PC4			
(a) *Schedule of Events – Group A*												
Timepoint (week)		0	2 wks after V1	6 wks (±14 d)	2 wks after V2	12 wks (±14 d)	2 wks after V3	18 wks (±14 d)	2 wks after V4	24 wks (±14d)		
Enrolment												
Informed consent	x	X^e^										
Check eligibility	x	X^e^										
Assessments												
Demographics/subject characteristics	x	x								x		
Family characteristics	x	x		x		x		x		x		
Medication, nutrition, exposure to smoking during pregnancy	x	x										

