Questionnaires Allergy (family members)	x	x										
Medical history, vaccination record	x	x		x		x		x		x		
Review AEs			x	x	x	x	x	x	x	x	x	x
Review concomitant medication	x	x	x	x	x	x	x	x	x	x	x	x
Nutritional characteristics^d^	x	x		x		x		x		x		x
Physical examination	x	x		x		x		x		x	x	x
SCORAD, EASI score		x		x		x		x		x	x	x
Palm lines documentation		x										
TEWL (Berlin)		x		x		x		x		x		
SPT										x		x
Stool scales^d^	x	x		x		x		x		x		
Postnatal hygiene score		x		x		x		x		x		
Pacifier questionnaire		x		x		x		x		x		
Palatability score^d^		x		x		x		x		x		
POEM score (Eczema)		x										
Skin swab infant (cheek)	x	x				x				x		
Skin swab caregiver (cheek)	x	x								x		
Skin swab caregiver (mamilla)	x	x				x				x		
Skin swab infant (body, interscapular)	x	x				x				x		
Oral swab infant		x				x				x		
Oral swab caregiver		x								x		
Stool sample infant	x	x				x				x		
Stool sample caregiver	x	x								x		
Blood draw		x								x	(x)	x
Dental status		X (Caregiver)								X (Child)		
Intervention												
Feeding of SP at site		x		x		x		x				x
Dispensation of SP		x		x		x		x		(x)^a^		x
Review compliance + tolerance of SP			x		x		x		x			x
OFC											x^a^	

Visit/Phone call	Enrolment/Screening		Reference period				V5	V5 solo^c^	(V6)^a^	Unscheduled Visit^b^
	V0 (optional)	V1	PC1		PC2					
(b) *Schedule of Events – Group B*										
Timepoint (week)		0	2 wks after V1		12 wks		24 wks (±14 d)			
Enrolment										
Informed consent	x	x^e^						x		
Check eligibility	x	x^e^						x		
Assessments										
Demographics/subject characteristics	x	x					x	x		x
Family characteristics	x	x					x	x		x
Medication, nutrition, exposure to smoking during pregnancy	x	x						x		
Questionnaires Allergy (family members)	x	x						x		
Medical history, vaccination record	x	x					x	x		x
Review AEs			x		x		x		x	x
Review concomitant medication	x	x	x		x		x	x	x	x
Nutritional characteristics^d^	x	x					x	x		x
Physical examination	x	x					x	x	x	x
SCORAD, EASI score		x					x	x	x	x
Palm lines documentation		x						x		
TEWL (Berlin)		x					x	x		x
SPT							x	x		x
Stool scale^d^	x	x					x	x		
Postnatal hygiene score		x					x	x		
Pacifier questionnaire		x					x	x		
Palatability score^d^		x						x		
POEM score (Eczema)		x						x		
Skin swab infant (cheek)	x	x					x	x		
Skin swab caregiver (cheek)	x	x					x	x		
Skin swab caregiver (mamilla)	x	x					x	x		
Skin swab infant (body, interscapular)	x	x					x	x		
Oral swab infant		x					x	x		
Oral swab caregiver		x					x	x		

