### Statistical methods

3.3

Diversity of the microbiome (primary endpoint) will be assessed utilizing alpha diversity calculations.^29^ The two study groups are compared using this diversity parameter. Moreover, based on the alpha diversity, other diversity indices like the Shannon diversity, the Gini‐Simpson index, or the evenness will be evaluated. No sample size calculation was performed due to the exploratory study design. *N* = 50 subjects per group is regarded as appropriate in order of magnitude of the few other studies in the context of pre‐chewing/saliva contact and/or microbiome analysis.^37^, ^38^, ^39^

In our explorative study, the primary efficacy analysis will be based on the full analysis set (FAS) and a secondary analysis will also be performed on the per protocol population (PPS) to assess the sensitivity of the analysis to the choice of analysis set. All safety analyses will be based on the full analysis set (FAS). The analysis will be performed without imputation of missing values. The significance level will be set to 0.05 (two‐sided). All other analyses will be considered explorative.

Univariable and multivariable logistic regression models will be performed for secondary binary endpoints (e.g., one diagnosed food allergy, food specific sensitisation, indices on microbiome diversity calculations). The analysis of secondary continuous endpoints (e.g., SCORAD, compliance over time) is conducted using analysis of covariance (ANCOVA). Child's sex, birth mode, number of siblings, pets, and other factors will be considered as covariates. Analysis will be carried out with the FAS. Based on the intention‐to‐treat (ITT) principle, the patients are analyzed according to the study group in which they started in.

Several explorative subcohort analyses (e.g., on antibiotic intake, infections) will be performed for the primary endpoint to find possible associations between covariates and diversity of the intestinal microbiome.

Selected secondary endpoints will also be analyzed with the PPS. The PPS is a subset of the FAS defined without participants with repeated insufficient consumption of the study product, defined as consumption <4 times/week (57%). As a general strategy, missing data will not be imputed in this study.

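### Table 1's exclusion for prior egg, peanut or hazelnut is not adapted to V5 solo infants, who are first enrolled at about one year, and their standing relative to Group B is left open

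*Protocol article*

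**What the plan says.** Section 2.2 and Table 1 set eligibility. The table is headed "Inclusion and exclusion criteria for Group A or Group B", so one list serves both groups. An infant is excluded if the following applies: "Previously consumed hen's egg, peanut, or hazelnut". No age or visit is attached. The single exemption, in the table's footnote, concerns milk: "Previous consumption of cow's milk, for example, as infant formula, is allowed".

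Section 2.3.1 describes V5 solo in these terms: "V5 solo consists only of V5 in Group B (and optional V6); participants will not have been enrolled before". Its purpose is also given: "This group serves as an additional reference group, as participants will not have been informed (biased) about premastication before". For Group B the timing of V5 is stated as follows: "Study participants will be invited for the end of study visit (V5) around the child's first birthday".

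In Table 3(b), the row "Check eligibility" is marked in the V5 solo column, as is informed consent. That column also carries the infant stool sample, blood draw, skin prick test, nutrition, medical history and concomitant medication. It is blank for adverse-event review and for the child's dental examination.

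Section 2.4.1 defines the primary comparison as Group A against Group B at V5. Section 3.3 plans 50 infants per group, without imputation of missing values, and states that "the patients are analyzed according to the study group in which they started in".

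**The concern.** The prior-consumption criterion makes sense for an infant who has not yet started solids. It makes much less sense for a child enrolled for the first time at about one year, after the period in which these foods would be introduced. If sites apply Table 1 as written, V5 solo becomes a sample of children who have eaten none of the three foods. V5 solo was added to give a reference free of one bias (parents having heard about premastication). The criterion would introduce another, selection on allergen exposure, which bears directly on the secondary endpoints of food-specific IgE and food allergy. If sites instead waive the criterion informally, they depart from Table 1, and the two centres may do so differently.

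A second ambiguity sits beside it. V5 solo is described both as part of Group B and as an additional reference, and the article does not say which description governs the analysis.

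**Working it through.** **Reproducing the plan's figure.** The only size given is 50 per group, and 50 + 50 = 100 agrees with the abstract. Section 3.3 says that no calculation lies behind it, so there is nothing further to reproduce. No number is given for V5 solo.

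**Age at which the criterion is applied.** Figure 1 puts V1 at 4 to 8 months, and Table 3 puts V5 at 24 weeks.
- 24 weeks = 24 × 7 / 30.44 = 5.5 months.
- Age at V5 = 4 + 5.5 to 8 + 5.5 = 9.5 to 13.5 months.
- With the ±14 days (0.46 month) allowed, the range is about 9.1 to 14.0 months.

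This fits the stated timing near the first birthday. A V5 solo infant therefore meets the criterion about 5.5 months later in life than an infant enrolled at V1.

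**The passages side by side.**
1. Table 1 applies to Group B, has no time anchor, and one exposure to any one of three foods excludes.
2. V5 solo is placed in Group B, and Table 3(b) marks the eligibility check in its column.
3. Group B solids follow current recommendations, subject to the parents' choice (section 2.3.1). Citing the same references, section 1.1.2 reads the evidence as favouring early and frequent feeding of allergenic foods, and says that egg should be given well heated.
4. The study imposes no dietary restriction on Group B (section 2.3.1).

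Points 3 and 4 make prior exposure to at least one food likely. Points 1 and 2 then exclude the exposed infant.

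**Recruitment, illustration only.** Let q be the share of one-year-olds who have had none of the three foods (assumed; the article gives no value). To enrol 25 such infants (also assumed), 25/q must be screened: 500 at q = 5%, 250 at 10%, 125 at 20%, 63 at 40%. Whatever q is, every infant enrolled under the literal rule has avoided all three foods.

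**Pooling, illustration only.** Suppose a share f of Group B's 50 were V5 solo infants whose mean differs from the rest by δ SD (both assumed). The A versus B contrast shifts by f × δ. With 50 per group and a common SD of 1, the standard error is √(2/50) = 0.20 SD. When Group A and enrolled Group B truly do not differ, the two-sided error rate is Φ(fδ/0.20 − 1.96) + Φ(−fδ/0.20 − 1.96).

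| f | δ (SD) | shift (SD) | error rate at nominal 0.05 |
|---|---|---|---|
| 0.1 | 0.2 | 0.02 | 0.051 |
| 0.2 | 0.5 | 0.10 | 0.079 |
| 0.5 | 0.5 | 0.25 | 0.24 |
| 0.5 | 0.8 | 0.40 | 0.52 |

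The effect runs from negligible to large, and nothing in the article says where in this range the trial would fall.

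**The case against.** The strongest reply is that this is an abridged protocol. Section 2.2 refers to Appendix S1 for more on eligibility, amendments were made during the trial, and the criterion may simply have been meant for V0/V1. That is plausible and cannot be ruled out. It does not remove the conflict in the published table, which names its scope, exempts one food explicitly and says nothing of V5 solo.

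Four stronger readings are tempting, and the defence is right to resist each.
- A reader might infer that one-year-olds cannot meet the criterion. The article gives neither an age nor an uptake rate for these foods and leaves feeding to the parents. Unlikely is as far as the text goes.
- A reader might infer that pooling with Group B is planned, or that the intention-to-treat sentence in section 3.3 puts V5 solo in the full analysis set. That sentence governs how participants are classified and does not define the set. The word additional in section 2.3.1 points towards a separate comparator.
- A reader might infer that the missing V1 sample damages the primary endpoint. The primary is a comparison at V5, and V5 solo infants do provide a stool sample then.
- A reader might infer that V5 solo would enter with zero events and dilute Group B's rates. Missing values are not imputed, so an unassessed infant is missing, not event-free. Medical history and medication are also recorded at that visit.

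The trial is moreover exploratory, and its discussion concedes both the bias from self-selected groups and its unsuitability for recommendations on allergy prevention.

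**Conclusion.** The eligibility conflict stands on the published text. A criterion suited to infants at the start of solids is applied, without adaptation, to a reference group first enrolled at about one year. Followed literally, it selects infants who avoided hen's egg, peanut and hazelnut, and this biases the additional reference on sensitisation and food allergy. The conclusion assumes that Appendix S1 does not adapt the rule; if it does, Table 1 still needs to agree with it. How many candidates would be excluded, and how far the endpoints would move, cannot be derived from the documents.

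The standing of V5 solo in the analysis is ambiguous rather than wrong. Harm to the A versus B comparison would arise only if these infants were pooled into Group B, and its size and direction are unknown.

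**What to change.** 1. Add a footnote to Table 1: the prior-consumption exclusion applies at V0/V1 and not at V5 solo, where earlier consumption of each food is recorded instead. The nutrition item already scheduled for V5 solo in Table 3(b) can carry this.
2. Add one sentence to section 3.3: V5 solo is analysed as a separate reference, outside Group B's N = 50 and outside the primary A versus B comparison.
3. In the same place, keep V5 solo out of the adverse-event and caries denominators, because neither adverse-event review nor the child's dental examination is scheduled for it.

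The cost is one footnote and one or two sentences. The only downside is fewer infants in Group B if pooling was intended. The change is best made before the V5 data are analysed, since a choice about pooling made afterwards would be open to the charge that the results guided it.

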**Methods:**

Two parallel study groups of infants at risk for atopic diseases (*N* = 100) are planned to be included. Healthy caregivers of eligible infants can decide to participate by either (A) introducing solids with additional provision of a sugar‐free ground biscuit suitable for pre‐chewing that contains increasing amounts of hen's egg, cow's milk, peanut, and hazelnut proteins or (B) by introducing solids following current feeding recommendations. The primary endpoint will be the assessment of the diversity of the infant's intestinal microbiome. Secondary endpoints will include an assessment of the acceptance of the feeding habit, the development of food allergies or food sensitization, and infections, including potential caries development, in association with the composition of the infant's oral microbiome.

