### Objectives

1.2

The primary objective is to compare the impact of different feeding habits on the diversity of the infant's intestinal microbiome. Infants will be introduced to solid food, either with reference to current recommendations as a reference group or by utilizing the traditional feeding practice, by pre‐chewing a sugar‐free ground biscuit in parallel to other weaning foods and breastfeeding (non‐randomized). Secondary objectives focus on the assessment of acceptance of the feeding habit; the development of allergic reactions, including food allergies and food sensitization; and infections, including observation of potential caries development, gastrointestinal problems, and thriving aspects.

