#### Intervention description

2.3.1

Mothers of both groups will be encouraged to continue breastfeeding while weaning foods are introduced stepwise to the infant's diet. Parents will decide in advance which group they would like to join, and—depending on the child's individual development—when first complementary foods are to be introduced (Figure 1). All participants will be informed equally regarding current feeding recommendations.^17^, ^21^

All Group A participants will visit the study site at five timepoints (V1–V5). Group B participants will visit the study site at two timepoints (V1 and V5). Blood samples will be collected at V1 and V5; SPT will be performed at V5 only. Samples for microbiome analysis will be taken at indicated visits. Telephone calls are scheduled 2 weeks after V1, V2, V3, and V4 (Group A) and 2 weeks after V1 as well as one interim phone call at week 12 (Group B).

All caregivers will be encouraged to keep a weekly diary recording frequency of pre‐chewing, tolerability, and palatability of solids introduction, as well as any adverse events, concomitant medication, and diet.

V0 (collection of stools + skin swabs) and V6 (enhanced diagnostic in sensitized subjects, including oral food challenges) are optional.

V5 solo consists only of V5 (and optional V6); participants will not have been enrolled before.

Group A – “Interventional/Pre‐chewing Group”: The mother (or one other previously determined caregiver) of an eligible infant will receive a sugar‐free ground biscuit once the infant starts eating complementary foods. The biscuit is ground to ensure homogeneity of the amount of included food proteins. These amounts will be increased by a factor of five in four stages, each lasting 6 weeks ±14 days, V1–V4 (Table 2). The actual amount of total protein of the allergenic food in the first dose at V1 (Table 2) starts slightly below calculated discrete ED05 values for the correspondent food allergens,^25^ which are 2.1 mg peanut protein, 3.5 mg hazelnut protein, 2.3 mg hen's egg protein, and 2.4 mg cow's milk protein. Further ingredients of the biscuit are wheat flour type 550 and margarine processed with rapeseed oil.

**TABLE 2 pai70147-tbl-0002:** Content of Peanut, Hazelnut, Hen's Egg, and Cow's Milk protein in the ground biscuit.

Group A	Visit 1–Visit 2	Visit 2–Visit 3	Visit 3–Visit 4	Visit 4–Visit 5/6

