#### Main secondary endpoints (for further endpoints, please see Appendix S1)

2.4.2

Compliance assessment/adherence of parents/caregivers conducting pre‐chewing via questionnaire on performance and frequency: query on a weekly basis, if performed daily; 4–7 times per week; <3 times/week (compliance defined as at least 4 days/week ≙ 57%)Composition of the oral microbiome and frequency of infant caries by 1 year of age (V5) according to the International Caries Detection and Assessment System (ICDAS, a clinical scoring system allowing detection and assessment of caries lesions and caries experience^30^)Frequency of IgE‐mediated food allergies to at least one of the four foods (hen's egg, cow's milk, peanut, hazelnut) after intervention by 1 year of age (V5) between Groups A and BAllergen‐specific IgE and IgG4 to hen's egg, cow's milk, peanut, hazelnut, Ara h 2, Cor a 14, and wheat at V1 and V5 in comparison between groups.Cumulative occurrence (frequency and severity) of respiratory and gastrointestinal infections (including oral infections) in comparison between groups

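### The V5 food-allergy comparison does not separate new cases from any that predate V1, and V1 food-specific IgE is not named as an adjustment variable

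*Protocol article*

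**What the plan says.** **Aim.** The Objectives (section 1.2) include "the development of allergic reactions, including food allergies and food sensitization". The Abstract likewise lists "the development of food allergies or food sensitization" among the secondary endpoints.

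**Endpoints.** Section 2.4.2 gives the frequency of IgE-mediated allergy to at least one of hen's egg, cow's milk, peanut and hazelnut at V5, compared between Groups A and B. A separate endpoint is specific IgE and IgG4 to these foods and to "Ara h 2, Cor a 14, and wheat at V1 and V5 in comparison between groups". Section 3.3 names food-specific sensitisation as an example of a binary secondary endpoint but gives no counting rule. Section 2.3.1 describes sensitisation when it sets out who is offered a challenge after V5: "In case of the detection of a food‐specific sensitization (elevated food‐specific IgE (>0.1 kU/L) or positive Skin Prick Test".

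**Baseline data.** Section 2.3.1 states: "Blood samples will be collected at V1 and V5; SPT will be performed at V5 only". At both visits, "blood samples from the infant will be collected and stored for allergy diagnostics". Participants in V5 solo have no V1 visit.

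**Eligibility.** Infants must be healthy and born at term. Table 1 excludes infants who have already eaten egg, peanut or hazelnut, or who have a diagnosed wheat allergy. It contains no criterion on sensitisation or allergy to the four study foods, and its footnote says: "Previous consumption of cow's milk, for example, as infant formula, is allowed".

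**Analysis.** Section 3.3 plans logistic regression for binary and ANCOVA for continuous secondary endpoints. On adjustment it says: "Child's sex, birth mode, number of siblings, pets, and other factors will be considered as covariates".

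**The concern.** An objective worded as development asks about onset after the intervention begins. A frequency at V5 measures status, which mixes onset after V1 with whatever was present at V1. Infants enter at 4 to 8 months (Figure 1). The Introduction says food allergy typically shows itself early in infancy, and section 4.1 provides for atopic dermatitis that exists at screening. Some sensitisation at V1 is therefore plausible. For cow's milk, exposure and even a reaction before V1 are possible.

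In a randomised trial this would mainly dilute the contrast. Here parents choose the group in advance (section 2.3.1), and their choice may be influenced by visible eczema or a suspected milk reaction. If V1 status differs between groups, the difference passes into the V5 frequencies and could be read as benefit or harm of pre-chewing. The variable that would reveal and largely correct this is already collected, but the plan does not commit to using it in the V5 models.

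**Working it through.** The article states no event rate, effect size or power, so there is no figure of its own to reproduce. From the article come 50 infants per group and a two-sided level of 0.05 (section 3.3). Every rate below is an assumption chosen to show direction and range.

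**Formula.** Let b be the share sensitised at V1 and i the share newly sensitised by V5 among those negative at V1. If V1 sensitisation persists, V5 prevalence is p = b + (1 − b) × i, and the share of V5 positives that predate V1 is b / p.

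**1. Share of V5 positives that are not new (i = 10%).**
- b = 5%: p = 0.05 + 0.95 × 0.10 = 0.145; share 0.05 / 0.145 = 34%
- b = 10%: p = 0.10 + 0.90 × 0.10 = 0.190; share 53%
- b = 20%: p = 0.20 + 0.80 × 0.10 = 0.280; share 71%

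**2. Equal V1 prevalence, true effect on onset** (i = 10% in A, 20% in B; true risk ratio 0.50). For the new-onset analysis, n per group is 50 × (1 − b).

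| b | V5 in A | V5 in B | Risk ratio at V5 | Power, V5 status | Power, new onset (ratio 0.50) |
|---|---|---|---|---|---|
| 0% | 10.0% | 20.0% | 0.50 | 29% | 29% |
| 5% | 14.5% | 24.0% | 0.60 | 22% | 27% |
| 10% | 19.0% | 28.0% | 0.68 | 18% | 26% |
| 20% | 28.0% | 36.0% | 0.78 | 13% | 24% |
| 30% | 37.0% | 44.0% | 0.84 | 11% | 21% |

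Power is low throughout. The message is that V5 status pulls the ratio towards 1, and that losing the V1-positive infants costs less power than keeping them.

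**3. Unequal V1 prevalence, no effect on onset** (i = 15% in both groups).

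| b in A | b in B | V5 in A | V5 in B | Risk ratio | Chance of a significant result favouring A |
|---|---|---|---|---|---|
| 5% | 10% | 19.25% | 23.5% | 0.82 | 7% |
| 5% | 15% | 19.25% | 27.75% | 0.69 | 17% |
| 5% | 20% | 19.25% | 32.0% | 0.60 | 31% |
| 10% | 20% | 23.5% | 32.0% | 0.73 | 16% |

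With no imbalance the last column would be 2.5%. With i = 10% and b = 5% versus 15%, V5 shows 14.5% versus 23.5%: ratio 0.145 / 0.235 = 0.62, odds ratio (0.145 / 0.855) / (0.235 / 0.765) = 0.55. In all these cases the new-onset ratio among V1-negative infants is 1, by construction.

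**The case against.** **The article is an abridgement.** Section 2.4.2 sends further endpoints to Appendix S1, and section 3.1.3 sends outcome definitions on allergy diagnostics and the food challenge there. A full counting rule may exist, so its absence from the article is not held against the plan. The mismatch, however, lies in what the article itself prints: objective, allergy endpoint, eligibility and parental choice.

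**The sensitisation cut-off is a trigger.** A reader might infer that section 2.3.1 defines a sensitisation endpoint counted from V5 status. It does not; it says who is offered a challenge. The point rests on the food-allergy endpoint in section 2.4.2.

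**Baseline IgE is not ignored.** It is compared between groups at V1 and V5, so an imbalance would be seen and IgE-based onset could be derived. The covariate list is also open-ended. Both stand, but showing an imbalance does not correct the binary endpoints, and an open list does not commit to this variable.

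**Prior disease is possible, not shown.** A reader might infer that sensitised infants are enrolled and existing disease is counted. The article only lacks an exclusion. Infants must be healthy and must not have eaten three of the four foods, so manifest prior allergy is mainly a cow's milk matter. Silent sensitisation could involve any of the four.

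**Sensitisation may resolve.** The persistence assumption excludes reversion, although supporting tolerance is a stated aim. This is a fair reason to keep V5 status as a description.

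**The consequence is limited.** These endpoints are secondary and explorative, and the Discussion disclaims prevention recommendations and concedes bias from open group choice.

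**Conclusion.** The concern holds in limited form. The V5 food-allergy comparison is a comparison of status under an objective of development, in groups formed by choice, with no exclusion of infants already sensitised or allergic to the study foods and no commitment to adjust for V1 IgE. Cases that predate V1 can count as outcomes, and a V1 imbalance would carry into V5.

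The size cannot be given. Under the assumed rates, equal V1 prevalence of 5% to 30% moves a true ratio of 0.50 to between 0.60 and 0.84, and an imbalance of 5 to 15 percentage points yields ratios of 0.82 to 0.60 with no effect. These figures depend wholly on the chosen rates and on persistence. The documents do not support saying that such an imbalance exists. The change is still worth making, because it uses data already collected and the Discussion presents the trial as a first step towards allergy-protective use of pre-chewing.

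**What to change.** 1. Name V1 food-specific IgE as a covariate in the V5 sensitisation and allergy models, and adjust V5 IgE and IgG4 for the log of the V1 value.
2. Add a new-onset analysis for each food among infants with V1 IgE at or below 0.1 kU/L to that food.
3. Do not count a food allergy diagnosed before V1 as new, and show cow's milk separately.
4. Report V5 status as prevalence. Keep V5 solo (no V1 blood) and infants positive on skin prick test alone (no V1 test) in that description.

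**Cost.** Only endpoint and analysis wording changes; no visit or sample is added. Slightly fewer infants contribute per food, and baseline status rests on IgE alone. If nearly all V1-positive infants remain positive, a yes/no baseline term can make the logistic fit unstable; the log value or the new-onset analysis is then preferable. Adjustment for V1 IgE does not remove other differences between self-selected groups.
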